**Fig. 2 Fig2:**
[figure not shown]
Flowchart of participants in the Community Trial

**Fig. 3 Fig3:**
[figure not shown]
Flowchart of participants in the MCI trial

#### Eligibility criteria

Participants or their representatives must give written, informed consent before initiating any study procedures (see Appendix 1 for Informed Consent Form).

##### Inclusion criteria

For all participants:

Age 60–80 years, to focus on individuals in the preclinical or early-risk stage for cognitive decline;Dementia Risk Score ≥ + 2 (LIBRA index) [74], to include participants with elevated dementia risk, in line with the preventive aim of the program;Elementary reading and writing skills, to ensure comprehension of intervention materials and participation in assessments;Basic digital literacy or access to a caregiver supporting videoconferencing, to enable participation in remote sessions and online components.

Community (cognitively intact) sample clarification: Participants recruited for the community arm are cognitively intact at baseline and do not meet MCI criteria. This ensures that the community sample represents preclinical or at-risk individuals without a formal diagnosis of MCI, clearly distinguishing them from the clinical trial group.

Additional criteria for participants with MCI (clinical arm):

Meeting one of the adapted CERAD criteria for very mild cognitive impairment [i) MMSE between 21 and 28 points, ii) memory learning task (3 × 16 words) of 25 words or less, iii) delayed recall: 75% or less];Clinical diagnosis of MCI as defined by the National Institute on Aging-Alzheimer’s Association workgroups - NIA-AA [75];Availability of a caregiver (living with or spending at least 10 h per week with the participant) to support participation and adherence. Participants without an available caregiver will still be eligible to receive the REMINDER program after the conclusion of the RCT.

###### Exclusion criteria

Exclusion criteria for both trials will include:

History of neurological or psychiatric conditions likely to affect cognition (e.g., stroke, major depression);Sensory deficits or mobility limitations preventing the effective delivery of the assessment or intervention;Significant functional deficits compromising engagement in program activities;Diagnosis of dementia, as the program is preventive.

#### Sample size

The sample size estimation was performed in “G*Power”, a statistical software program. Power analysis was performed and was based on both existing data on the effects of dementia risk reduction programs in a cognitive composite [28, 76] as well as in our preliminary feasibility study results that held small to medium effects (f >0.20). Accordingly, for the Community trial, a total sample size of 244 was determined based on an expected power of 0.80 to detect small to medium effects (f >0.20) in comparison analyses in the primary outcomes (e.g., cognitive composite; lifestyle change) (G*Power). Considering an expected dropout rate of 10%, a total sample size of 268 participants leads to an approximate required final expected sample size of 270 (90 per arm). For the Clinical Trial, the same power analysis was performed, and considering now three arms, a final sample size of 270 is distributed across arms, with 90 participants per arm.

Given the multifactorial higher risk of women developing dementia, we will take this into account in the sex/gender ratio of the sample recruited as well as in the efficacy analyses.

#### Recruitment

For the Community trial, potential participants will be contacted through traditional and social network advertisement (Project’s website - www.remindereomeucerebro), as well as through community and clinical recruitment settings with established protocols with the University of Coimbra (Coimbra University Hospitals, Memory Clinics, Elderly Day Care Centres, and Senior Universities in the Coimbra region). Interested individuals will first be contacted by a trained member of the research team, either by phone or in person, to provide detailed study information and conduct an initial eligibility screening. Those who appear eligible will be invited to an in-person meeting, where full eligibility will be confirmed, written informed consent will be obtained, and participants will complete the baseline assessment before random assignment to study arms.

For the Clinical trial, general hospitals from three Portuguese regions (Coimbra, Trás-os-Montes, Porto) will be approached (following approval from each Local Health Unit’s ethics committee). Doctors will identify and signal patients with a diagnosis of MCI. These patients will then be approached by a member of the research team, who will explain the study, conduct the screening (during a clinic visit), and schedule the baseline assessment for those eligible. After signing written informed consent, participants will complete the baseline evaluation and will then be randomly allocated to the study arms.

In both trials, study ID numbers will be assigned by a research team member using a pre-generated list of random numbers. These IDs are used solely for anonymization and data management purposes, and are unrelated to the randomization of participants into study arms.

Recruitment is anticipated to begin in January 2026, with data collection (including pre- and post-intervention assessments and follow-up assessments at 3, 6, and 18 months) expected to continue until approximately mid-2027.

### Assignment of interventions

Once participants meet all inclusion criteria and provide informed consent, they are assigned a unique study ID number. For randomization, a predetermined set of study ID numbers is allocated to each recruitment site based on the expected recruitment ratio. Randomization is then performed by a researcher blinded to assessment procedures using a computerized random number generator, assigning participants to their respective study groups: Community Trial - REMINDER face-to-face, REMINDER virtual, or Waitlist Control and Clinical Trial - REMINDER alone, REMINDER + caregiver support, or Waitlist Control. This process ensures allocation concealment and prevents bias in group allocation.

#### Implementation

Recruitment staff request the randomization from the central study team and receive a form with the assigned randomization number, which is forwarded to another team member responsible for informing the participant. Participants are then notified of their assigned group. Throughout this process, recruitment staff and outcome assessors remain blinded to the allocation, maintaining the integrity of the trial.

#### Blinding (masking)

A blinded trained neuropsychologist will perform the neuropsychological assessment at the predicted time points, and another trained clinical neuropsychologist will deliver the REMINDER program under the supervision of the PI and remaining research team, distributed across recruitment sites. This researcher and the study coordinator will be responsible for database creation and completion, and the remaining research team will perform the data analysis.

#### Statistical methods

Statistically, we will analyse the program efficacy following intention-to-treat (ITT) and per-protocol (PP) principles following CONSORT recommendations [77], allowing to examine data from all randomized participants for the two trials (even those with missing values on outcome measures). Linear mixed models (LMMs) will be conducted to determine the effects of the intervention over time (time × group interaction effects) on primary and secondary outcomes. LMMs have been chosen as the primary method for analyzing repeated measures data, as they account for within-subject correlations over time, allow inclusion of fixed and random effects, and handle missing data under the missing-at-random assumption. Given that our primary and secondary outcomes are continuous variables, LMMs are appropriate. Should exploratory analyses indicate non-normality or different data distributions, alternative mixed models (e.g., generalized linear mixed models) will be considered to ensure model adequacy. Participant characteristics, including age, sex/gender, education level, baseline cognitive performance, baseline dementia risk, and adherence to the intervention (attendance and engagement in sessions), will be included as covariates to account for potential confounding effects on outcomes. Additional statistical analyses such as two-wave latent change score models, reliable change index, Chi-square tests, and within-group effect sizes will be performed, as well as a mediator and moderator analysis. The generalized estimating equation (GEE) method will be used to analyse the estimated regression coefficients (i.e., the effect estimates) for these outcomes (functionality, global cognition, dementia risk score) concerning neurobiological data (neural plasticity and NfL). The GEE method extends standard regression analysis, accounts for the correlation between repeated measurements, and is more robust to violations of normality. For exploratory analyses of diagnostic transitions (e.g., from cognitively intact to MCI or dementia), Markov models will be employed to estimate transition probabilities and characterize patterns of change across follow-up. Initial data analysis will be done using IBM SPSS Software, version 28.0 (IBM Corp, Armonk, NY, USA), and more advanced modeling will be performed using R Program (R Core Team, 2022).

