The REMINDER intervention combines 20 group sessions (with an approximate length of 60–75 min) twice weekly over 10 weeks. To ensure cultural relevance and engagement, sessions integrate Portuguese-specific elements, such as song lyrics from the Festival da Canção, references to the 25th of April revolution, and discussion prompts related to participants’ autobiographical experiences. The content of sessions will integrate brain health psychoeducation, cognitive training, the practice of compensatory memory aids, personally meaningful goals management training, and stress management techniques (see Fig. 1 for the conceptual model of the REMINDER intervention and Table 1 for detailed session contents). Specifically, a set of contents and structures were designed to address existing gaps in the literature. Namely, to overcome low adherence, the program includes interactive and personalized sessions, including strategies like goal setting and mindfulness drawing from previous work with these populations [43, 46], as well as motivational strategies (motivational interviewing, positive reinforcement, and progress tracking) to encourage adherence. In addition, to target specifically the psychosocial risk factors (stress, social isolation, depression, among others) [47], we incorporated stress management techniques based on scripts from compassion-based therapies as well as relaxation techniques [48, 49], social interaction and support and emotion regulation strategies (e.g. attention deployment, positive cognitive reappraisal, reframing speech training). Believing that merging the brain, these behavioral strategies in a dementia risk reduction program will foster individuals’ mental health and build their capacity to draw on improved psychological and cognitive reserve to prevent and cope with remaining risk factors.

A manualized protocol was developed to provide standardized elements and detailed guidelines for program delivery. Health professionals (psychologists, neuropsychologists) delivering the intervention will receive training using the manual before to implementing REMINDER. Postdoctoral-level clinical psychologists from the research team members will lead the interventions in both delivery modes (face-to-face and virtual). To minimize bias, the professionals delivering the program will be counterbalanced across the two delivery methods.

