##### REMINDER4carers arm

This experimental arm is offered only to MCI participant’s caregivers, who will receive ten parallel psychoeducation and support sessions alongside the delivery of the REMINDER program to the patients. Sessions will be delivered weekly, in groups of 5–8 caregivers, lasting approximately 60 min each, either face-to-face or virtually depending on caregiver’s availability. The sessions will provide emotional support and guidance on caregiving topics such as changing roles, uncertainty of care needs, future and long-term planning, caregiver well-being and self-care, communication skills, and grief and loss.

Research also indicates that increasing caregivers’ awareness of patients’ needs and promoting supportive behaviors enhances patients’ adherence and engagement in protective health behaviors (e.g [35]).,. Moreover, caregivers themselves are at increased risk of cognitive decline and dementia due to chronic stress and caregiving burden [50]. These sessions also aim to promote caregivers’ own well-being and resilience, indirectly supporting their cognitive health.

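### REMINDER is delivered in groups, but neither the stated sample size nor the mixed model as described allows for correlation within a delivery group

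*Protocol article*

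**What the plan says.** Delivery is collective: "The REMINDER intervention combines 20 group sessions", twice weekly for 10 weeks. The Background and rationale section lists peer support and group interaction among the means by which the program should work. The size of the patient groups is not given. The only group size in the article is for carers: "Sessions will be delivered weekly, in groups of 5–8 caregivers". The waitlist arms have no active intervention until after the 6-month follow-up and are then offered REMINDER.

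The Sample size section reports "a total sample size of 244 was determined" for the Community Trial, with an "expected power of 0.80 to detect small to medium effects (f >0.20". The only inflation is for attrition: "Considering an expected dropout rate of 10%, a total sample size of 268 participants", rounded to 270. The Clinical Trial repeats the same calculation: "a final sample size of 270 is distributed across arms, with 90 participants per arm".

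Under Statistical methods, linear mixed models are chosen "as they account for within-subject correlations over time, allow inclusion of fixed and random effects". The covariates named are participant characteristics and adherence. The GEE analyses are likewise justified by correlation between repeated measurements. No delivery group or facilitator term is named.

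**The concern.** Participants are randomised one by one, but those in the active arms are then treated together and are meant to influence one another. A group that works well, or has a stronger facilitator, shifts all its members in the same direction. Repeated-measures terms capture correlation within a person and do not capture this. Up to month 6 the waitlist is not grouped, so the clustering is partial: it inflates the variance of the active-arm means only.

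Two things are at stake in both trials. A model without a group term would give active-versus-waitlist intervals that are too narrow and a type I error above 5%. And the 0.80 power claim, which assumes independence, would be optimistic once the clustering is modelled properly.

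**Working it through.** **Inputs from the article (Trials design, Sample size).** Three arms, 1:1:1, f = 0.20, power 0.80, 244 evaluable, 10% dropout, 270 enrolled.

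**Inputs assumed.** Alpha 0.05 (not stated). Patient group size m = 8, with 5 and 10 as alternatives. ICC 0.01 to 0.10. The article gives no figure for either m or ICC.

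**Step 1: reproduce the plan's figure.** For a one-way ANOVA of k = 3 independent groups, the F statistic has 2 and N − 3 degrees of freedom and noncentrality N·f². The smallest N with power of at least 0.80 is 244 (power 0.8002). Alternative designs do not give 244: two groups give 199 and four give 277; at correlation 0.5, a repeated-measures between-group test gives 184 (two time points) or 148 (five). So 244 contains no allowance for clustering. Dropout: 244 × 1.10 = 268.4, the stated 268. Enrolling 270 leaves 270 × 0.9 = 243, with power 0.798, so there is no slack.

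**Step 2: type I error, active versus waitlist, group ignored.** Design effect in a grouped arm: DE = 1 + (m − 1)·ICC. With one grouped and one ungrouped arm of equal size, true variance over naive variance is (DE + 1)/2. At m = 8 and ICC 0.05, DE = 1 + 7 × 0.05 = 1.35 and the ratio is 2.35/2 = 1.175, so the naive standard error is 1/√1.175 = 0.92 of the true one. Type I error is then 2·[1 − Φ(1.96/√1.175)] = 0.071. Simulation (10 groups of 8 versus 80 independent controls) agrees:

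| ICC (m = 8) | DE | Variance ratio | Type I error, formula | Type I error, simulation (about) |
|---|---|---|---|---|
| 0.01 | 1.07 | 1.035 | 0.054 | 0.055 |
| 0.02 | 1.14 | 1.07 | 0.058 | 0.057 |
| 0.05 | 1.35 | 1.175 | 0.071 | 0.070 |
| 0.10 | 1.70 | 1.35 | 0.092 | 0.093 |

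With 5 per group the formula gives 0.052, 0.055, 0.062 and 0.074.

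**Step 3: power of the planned 270.** Two of the three arms are grouped, so the mean inflation is (2·DE + 1)/3 and the effective N is 243 divided by it. At m = 8 and ICC 0.05: (2.70 + 1)/3 = 1.233, and 243/1.233 = 197. This effective N goes into the Step 1 formula, with no gain from baseline adjustment.

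| ICC | Power, m = 5 | Power, m = 8 |
|---|---|---|
| 0.01 | 0.79 | 0.78 |
| 0.02 | 0.78 | 0.76 |
| 0.05 | 0.74 | 0.70 |
| 0.10 | 0.69 | 0.62 |

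At m = 10 power is 0.77, 0.68 and 0.58 at ICC 0.01, 0.05 and 0.10.

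**Step 4: active versus active.** If the two active arms are treated in separate groups, both sides carry DE and the variance ratio is DE itself. At m = 8, type I error is about 0.067, 0.092 and 0.13 at ICC 0.02, 0.05 and 0.10. If patients of both arms sat in the same groups, the group effect would cancel: a simulation with half of each group from each arm gives 0.047, 0.046 and 0.039, slightly conservative.

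**The case against.** The best defence is that the model is not fully specified here. A mixed model can hold a group random effect, the article does not exclude one, and a statistical analysis plan that is not shown may contain it. That stands as far as it goes: a reader might infer that the trial's standard errors will be too small, but the article shows only that the dependence it names is within-subject. The statement must stay conditional on no group term being fitted and on an ICC above zero. The sample size is different. It is fixed in the article, reproduces exactly under independence, and no later analysis document changes how it was derived.

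Four other limits also stand.

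- **Site.** A reader might add recruitment site as a cause, since "a predetermined set of study ID numbers is allocated to each recruitment site based on the expected recruitment ratio". Randomisation is individual, so omitting site need not shrink the standard error of an arm contrast, and adding a site term would not cure group clustering.
- **Active versus active.** It is tempting to say the error is always worse here. The article does not say whether Clinical Trial patients in the two active arms attend separate groups, and carer sessions run in parallel to the patients' program. In the Community Trial, facilitators are counterbalanced across delivery modes, so facilitator variance partly cancels, and the objectives and hypotheses do not name that contrast.
- **Baseline adjustment.** The 0.80 assumes no gain from it, yet baseline cognition is a planned covariate. At m = 8 and ICC 0.05, if that ICC applies to the adjusted residual, a baseline–outcome correlation of about 0.43 would offset the loss, and at 0.5 power would be about 0.83. That correlation is also an assumption.
- **Size.** At ICC 0.01 the effect is close to negligible. The calculations are for a single time point, not the planned time-by-group model.

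**Conclusion.** The concern holds in conditional form. The article describes a group-delivered intervention, a sample size that assumes independent participants, and a model rationale that names only within-subject correlation. If the therapy-group ICC is above zero and no group term is fitted, active-versus-waitlist standard errors are too small: with 8 per group, a naive-to-true ratio of about 0.98 at ICC 0.01, 0.92 at 0.05 and 0.86 at 0.10. The effect is minor at ICC 0.01 to 0.02 and material from about 0.05. If clustering is modelled, the 0.80 power becomes roughly 0.62 to 0.79 over ICC 0.01 to 0.10 with 5 to 8 per group, before any gain from baseline adjustment. All these sizes rest on the assumed group size, ICC and alpha.

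The documents do not support three stronger readings: that the standard errors are certain to be wrong, that site contributes, or that comparisons between active arms are worse whatever the group composition. Nor is the waitlist unclustered throughout. Its participants may attend REMINDER groups after month 6, and 18 months is a time point for the primary outcomes.

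**What to change.** 1. Record a delivery-group ID and a facilitator ID for every participant, including waitlist participants who later take up the program and, in the carer-support arm, the carer group. Recruitment is anticipated from January 2026, and these are easy to capture prospectively and hard to reconstruct.
2. Fit a partially nested mixed model: a random effect for delivery group in the group-treated arms, facilitator where estimable, and small-sample degrees of freedom. Treat waitlist participants as unclustered only up to month 6. For the 18-month data, assign those who attended REMINDER to their delivery group.
3. State the planned patient group size and whether the two active arms in each trial are treated in separate groups.
4. Keep N at 270 per trial and restate power over an assumed ICC range such as 0.01 to 0.10, showing any gain from baseline adjustment as a separate, explicit assumption.

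The cost is two ID fields (three in the carer-support arm), one or two extra random terms, somewhat wider intervals and a less favourable stated power.

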## Discussion

Dementia prevention trials may benefit from prioritizing healthy lifestyle interventions, given emerging evidence of their potential impact. The REMINDER program integrates evidence-based strategies from prior multidomain trials, including goal setting, lifestyle psychoeducation, cognitive training, emotion regulation, and social engagement, and adapts them within a holistic neuropsychological rehabilitation framework. Previous feasibility testing of REMINDER in a small community sample demonstrated high adherence and preliminary benefits on cognition and lifestyle behaviors, suggesting that the program is acceptable and feasible for older adults at risk of dementia.

A distinctive feature of REMINDER is it emphasis on psychosocial risk factors, such as depression, stress, and social isolation, which remain underrepresented in most dementia risk reductions trials. By combining cognitive and emotional strategies with opportunities for peer interation and support, the program is designed to foster engagement, sustain motivation, and encourage the adoption of healthier lifestyle bahviors. Goal setting and monitoring, in particular, may help participants translate program content into everday prative, supporting adherence across time.

A recent clinical trial by Mace et al. (2024), has further highlighted the importance of addressing psychosocial and mental health risk factors in dementia prevention, signaling an important shift in the field. Notably, the REMINDER program was conceived and developed in 2022, prior to the publication of such evidence, and thus reflect an early commitment to integrating these components into a multidomain framework. While both approaches recognize the relevance of psychosocial risk factors, REMINDER is distinctive in its explicit grounding in holistic neuropsychological rehabilitation principles and its cultural adaptation to the Portuguese context, with an emphasis on goal setting, peer support, and the integration of cognitive and emotional strategies. In this sense, the emerging literature reinforces rather than diminishes the novelty and value of our approach.

Despite this promise, several potential challenges should be considered. Participant adherence may vary depending on individual motivation, baseline cognitive status, and availability of caregiver support. The collection of blood biomarkers may be limited by logistical or acceptability constraints. Additionally, cultural and socioeconomic factors specific to the Portuguese context may limit the generalizability of findings.

The planned RCT will expand upon prior feasibility work by including both community-dwelling older adults and individuals with MCI, allowing examination of program applicability across different risk profiles. In addition to cognitive and psychosocial outcomes, the study will also explore biomarker changes, providing insight into potential mechanisms of action. Together, these findings will contribute to the broader literature on dementia prevention, particularly in culturally and demographically underrepresented populations, and may inform the design of future holistic, multidomain prevention programs.

